**Potential Benefits**

All respondents will have the opportunity to view web links to HIV/STI, drug, alcohol, and mental health treatment at the end of both surveys and will be given an option of writing (either anonymously or by providing an email address for a response) their reactions to the survey and directing questions to the principal investigator ([name]). We successfully used this format in all of our prior online studies. Only a small proportion of participants (about 1%) have chosen to directly contact the investigators.

Benefits to society in general are anticipated through the dissemination of intervention findings (i.e., regarding high-risk sexual behavior and drug use). Results will inform local and national public health agencies about the magnitude of these problems and help them to develop outreach and prevention strategies that target Internet users, as well as the local community. Potential benefits of this type of Internet-based intervention approach include its efficiency, cost-effectiveness, and ability to be replicated.

Study Timeline

| **Date** | **Deliverables** |
| --- | --- |
| 10/06 – 05/07 | Develop Intervention Protocols |
| 10/06 – 05/07 | Develop Instruments (with consensus between CDC and Sites) |
| 10/06 – 05/07 | Develop Data Management/Sharing Plans |
| 12/06 – 06/07 | Develop Intervention Materials (e.g., videos, web pages) |
| 05/07 – 06/07 | Work with CABs/expert Advisory Groups |
| 07/07 | Submit IRB Packages to Prevention Research Branch |
| 07/07 – 09/07 | Submit IRB Packages & Obtain Approvals (Local and CDC) |
| 09/07 – 10/07 | Implement Pilot Intervention Testing |
| 10/07 – 11/07 | Fine-Tune Intervention |
| 12/07 | Submit IRB Amendments & Obtain Approvals |
| 1/08 – 5/08 | Recruit & Enroll Intervention Participants and Implement Intervention |
| 5/08 – 10/08 | Follow-up Participants (60 days post-baseline) |
| 10/08 – 12/08 | Data Cleaning & Verification |
| 01/09 – | Data Analysis |
| 01/09 – | Disseminate Findings |

**Internet Banner Ad Clicks (N=19,486)**

**Meet Criteria for Intervention Inclusion (49%=4,125)**

**Consent to participate in baseline survey (54%=10,522)**

**Complete Baseline Survey** **with Programmed Screening Questions (80%=8,418)**

**Computerized Randomization**

**YES**

NO

Survey Exit Page

**YES**

NO

Survey Exit Page

**Attrition 30%~420**

**Attrition 30%~420**

**Branch 2**

**20%=600**

**Branch 3**

**20%=600**

**Branch 4**

**20%=600**

**Attrition 30%~420**

**Branch 1**

**20%=600**

**Control**

**60-day follow-up survey**

**Attrition 40%~360**

**60-day follow-up survey**

**60-day follow-up survey**

**60-day follow-up survey**

**Complete Post-Intervention Survey (Intentions to Change Behavior)**

**Attrition 40%~360**

**Standard Prevention Webpage**

**‘Morning After’ Video**

**‘Talking About HIV Video’**

**Both Videos**

**Branch 5**

**20%=600**

**60-day follow-up survey**

**Consent to give email and be followed (73%=3,000)**

**Study Design for 5-Branch Randomized Controlled Trial**

Number of Online Ad Impressions Potentially Viewed = 847,217

Model estimates are based on a previously conducted online survey of MSM.26 The click-through-rate (CTR) was 2.3% on Manhunt.net, yielding the Banner Ad Click estimate (clicks/impressions=CTR).45 The estimate for consenting to give an email address and participate in the intervention is based on the online pilot intervention.46

**STUDY POPULATION**

## General Description

### The overall study population will consist of approximately 10,500 MSM. The study sample for the intervention (those randomly assigned to branches 1-5) will be 3,000 MSM who reside in the United States, are age 18 and over, who have reported oral or anal sex with any male (new partner or not) in the past 60 days AND reported oral, anal or vaginal sex for the first time (new partner) with a male or female within the past 60 days, and who represent diverse race/ethnicities and geography.

## Intervention Participant Inclusion Criteria

• Male;

• Age 18 and over;

• Ability to read and respond in English;

• Reside within the United States;

• Report oral or anal sex with any male (new partner or not) in the past 60 days AND reported oral, anal or vaginal sex for the first time (new partner) with a male or female within the past 60 days;

• Complete baseline survey

• Provide an email address;

The recruitment web site will be a subscription-based adult site that requires users to confirm that they are 18 years or older when registering. The study consent form explicitly states that men must be 18 or older to participate. However, this is an internet-based study and therefore the study team will be unable to verify the validity of inclusion criteria, including age.

The only inclusion criteria that will be shared with participants (in the consent form) is gender, age, residence in the U.S., and “sex with another man.” The detailed behavioral inclusion criterion for participation in the intervention trial will be measured in the context of the baseline survey. The likelihood of potential participants learning the criteria and returning to the site to retake the survey will be minimized. The research team will be able to identify duplicate email addresses and determine appropriate action during the data cleaning phase of the project. However, the research team does not anticipate that this will be a significant issue given that study activities represent time away from an individual’s recreational internet activities.

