Email addresses and data security: An email address will be the only identifying information collected; however, the email address will be encrypted and stored separately from survey data. Email addresses will be stored in an electronic file separate from survey data on a secure, firewall protected Public Health Solutions-managed server. Only the Public Health Solutions Manager of Web Development and Programming will have access to these files. If email addresses were inadvertently released, they would be un-readable. After all of the 60 day follow-up surveys have been completed, the encrypted email addresses will be destroyed. For those respondents who do not respond after 3 email follow-up attempts, we will delete the email address when their follow-up window expires. Other than email address, no other personally identifying information will be collected. No client-side persistent cookies will be used. For example, no cookies will be left on the user’s computer between the time of baseline and 60-day follow up.

Data will be stored on the Public Health Solutions, Data Link password protected server and will not be accessible by any persons who are not directly involved in the research. The server is protected by firewalls and other safeguards. Only members of the research team will have access to the data. Data will be backed up regularly and stored securely according to Public Health Solutions disaster recovery and business continuity protocols.

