**Data Collection Procedures**

As participants complete each section of the online survey, the data will immediately be transferred to a Public Health Solutions designated server that cannot be accessed publicly. At the completion of data collection, an analytic file will be prepared by the Manager of Web Development and given to the data analyst in the Research and Evaluation Unit. The survey file, which has no personal identifiers, will be removed from the server and stored in a secure site. Only the study investigators and CDC collaborators will have access to the data. Because the analytic file has no personal identifiers, a CD will be kept in a locked file in the PI’s office for up to 10 years.

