**Protection of Privacy/Confidentiality**

Participants will be assigned a unique study number. Behavioral survey (baseline, immediate post-intervention, 60-day follow-up) data will only include this unique study number. Email addresses of participants who agree to provide this information will be stored in an electronic file separate from survey data on a secure, firewall protected Public Health Solutions-managed server. The electronic file will contain email addresses linked to a participant’s unique study number. This linking file is necessary to identify and contact participants for the 60-day follow-up survey and track the result (i.e., completed follow-up or not). This file will be destroyed after the data collection period (i.e., 60-day follow-up assessments have been completed). Only the Public Health Solutions Manager of Web Development and Programming will have access to these files. Even in the highly unlikely event of a breach of the security system, the survey data exist only as a string of numbers with a few qualitative responses. The analytic data file has no personal identifiers and access will be limited to study staff.

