**Data Management**

Public Health Solutions will utilize a web-based data monitoring tool to track recruitment and survey completion. There will be no way to identify participants using this tracking tool. Public Health Solutions will regularly report tracking tallies (with no person-level identifiable data) as the data collection period progresses. The assessment data will be encrypted and transferred routinely to CDC using a secure data network system. As in all of our other online studies, after data collection, we will thoroughly clean and conduct contingency checks on the data to ensure high quality of data, in terms of completeness and accuracy. We will report on the overall completion rate for the intervention, as well as the different steps in the consent process. The data will be released in SPSS and SAS formats to other investigators, although the data can be converted to other statistical software packages, such as STATA. We may require a data-use agreement with interested parties, depending on the variables being requested and whether the requested data have already been published or not. After cleaning and analyzing the data, we will report the strengths and limitations of the dataset, in terms of recommendations for data analysis, reporting, and interpretation.

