**Quality Assurance**

After data collection, data will be checked for reliability and validity of value entries, and consistency across data elements. Since the provision of an email address is a requirement for participation in the intervention study, it is unlikely that duplicate records will be an issue for this study. However, the study team will be unable to identify if an individual has enrolled into the study more than once using differing email addresses. Should this occur the duplicative data will likely remain in the data file. This occurrence is likely to be infrequent, considering the lack of a large incentive. All quality assurance measures taken during data collection will be documented and made available to collaborators. Finally, to guard against bias in the analysis and interpretation of the data, analyses will be performed and reviewed by both scientists at Public Health Solutions and CDC.

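### The protocol does not keep email addresses until its own duplicate check: about a third are deleted earlier, and nothing holds the rest until the check is done

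*Protocol*

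**What the plan says.** **The check.** Intervention Participant Inclusion Criteria states: "The research team will be able to identify duplicate email addresses and determine appropriate action during the data cleaning phase of the project". Data Management places cleaning late: "after data collection, we will thoroughly clean and conduct contingency checks on the data". The Study Timeline dates cleaning 10/08 to 12/08, with enrolment in 1/08 to 5/08 and follow-up in 5/08 to 10/08.

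**The deletion rules.** Protection against Risks has two. For non-responders: "For those respondents who do not respond after 3 email follow-up attempts, we will delete the email address when their follow-up window expires". For everyone else: "After all of the 60 day follow-up surveys have been completed, the encrypted email addresses will be destroyed". Protection of Privacy/Confidentiality adds, of the file linking addresses to study numbers: "This file will be destroyed after the data collection period". Only the web development manager has access to these files. The file for analysis carries no address; Data Collection Procedures says: "The survey file, which has no personal identifiers, will be removed from the server and stored in a secure site".

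**The reliance on email.** Quality Assurance gives the required email address as its reason for expecting few duplicates. It concedes only that repeats under different addresses would go unseen and stay in the data. Recruitment and Randomization Procedures describe automatic assignment after the second consent and mention no comparison with addresses already enrolled.

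**The concern.** A same-address repeat is the one kind of duplicate the protocol could detect, and its text implies that it will. The check needs both addresses of a pair to exist when it is run. One stated rule removes a large share of them beforehand, and no rule holds the others until the check is finished.

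A repeat also does its damage at randomisation. A man assigned a second time may have seen two conditions. If he answers only one of his two follow-up invitations, his outcome is credited to one branch although he was also exposed to another, and his unanswered entry counts as a randomised man lost to follow-up. Once the address behind that entry is deleted, no later cleaning step or analysis plan can recover the link.

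The loss is also uneven. The protocol expects more non-response in branches 1 and 2 than in branches 3 to 5, so the chance of finding a duplicate would depend on the branches assigned and on whether the man responded.

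**Working it through.** There is no plan figure to reproduce for the duplicate check. The working compares the order of the steps and then counts the addresses affected.

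**1. Order for non-responders.**
- Cleaning follows data collection (Data Management), so every individual follow-up window has closed by then.
- The dates agree. The last enrolment month is 5/08. Informed Consent Procedures gives a maximum of 75 days for completing follow-up and, separately, a further 21 to 30 days of reminders after day 60, so at most 60 + 30 = 90 days. Counted from 31 May 2008, these limits fall on 14 August and 29 August, before cleaning opens in 10/08.
- Deletion therefore precedes the check.

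**2. Order for men who complete follow-up.**
- Destruction comes after all follow-up surveys are completed.
- Cleaning comes after data collection.
- Both steps have the same starting point and their order is not fixed.

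**3. Addresses deleted before the check.** Inputs are from Attrition and Retention Efforts: 240 (40%) in each of branches 1 and 2, and 180 (30%) in each of branches 3 to 5.
- 2 × 240 + 3 × 180 = 480 + 540 = 1,020; 1,020 / 3,000 = 34%.
- Addresses left: 3,000 − 1,020 = 1,980.
- At the 70% retention in the sample-size section: 0.30 × 3,000 = 900 deleted (30%) and 2,100 left.

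**4. Chance that a second randomisation gives a different branch.** Randomization Procedures gives 1 in 5 per draw. For two independent draws: 1 − 5 × 0.2² = 1 − 0.20 = 80%. The balancing rule barely changes this. With two groups at 22.5%, two at 17.5% and one at 20%, the result is 1 − (2 × 0.225² + 2 × 0.175² + 0.20²) = 79.75%.

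**5. Share of same-address pairs that can no longer be matched.** This assumes that deletion is by study number, and that a man's two entries respond independently at the overall rate of 66% (1,980 / 3,000).
- At least one address gone: 1 − 0.66² = 56%.
- Exactly one follow-up answered: 2 × 0.66 × 0.34 = 45%.
- By branch: 1 − 0.7² = 51% if both entries are in branches 3 to 5; 1 − 0.6² = 64% if both are in branches 1 and 2.

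Independence is doubtful within one man. If he always responds to both invitations or to neither, 34% of pairs lose an address and none has exactly one answer. If no man ignores both invitations, 2 × 0.34 = 68% lose one address, and all of these have exactly one answer.

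**6. Number of repeats.** The protocol gives no rate and no figure from which one could be derived. The percentages in step 5 apply to pairs, not to the 3,000 men.

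**The case against.** A reader might infer that every address is destroyed before cleaning, so that the check cannot be run at all. The text does not say that. For men who complete follow-up, running the check first and destroying the addresses afterwards would satisfy every section. Restricted access is no barrier either: the web development manager holds the linking file and also prepares the analytic file, so that role could flag duplicate study numbers before handover. This part of the objection stands.

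A reader might also infer that one man will appear as two independent people in the 60-day comparisons. For that he must complete follow-up under both entries. Neither address then falls under the early deletion rule, and the pair can still be matched if the check comes first. The pairs certain to be lost contain at least one non-response.

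The protocol also gives reasons to expect few repeats: no payment, a long survey, and little information about the other conditions. Nothing in it supports a particular repeat rate, or the idea that control participants return to obtain content.

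Finally, the rule for handling a duplicate once found may properly sit in an analysis or data management plan. That is fair, and its absence here is not the point. A later plan cannot restore a deleted address, so the early deletion of non-responders' addresses remains in conflict with the check.

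**Conclusion.** The concern holds in a limited form. For non-responders, 30% to 34% of enrolments on the protocol's own figures, a stated deletion rule defeats a stated safeguard. For the rest, the protocol leaves the order of checking and destruction open and does not require the addresses to be kept until the check is done. No earlier check is described.

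The consequences are a possible outcome credited to one branch after exposure to another, and inflated randomised counts and attrition. Double counting of outcomes follows only if the remaining addresses are destroyed before the check.

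The 34% rests on the protocol's attrition forecast and the 80% on independent draws at 1 in 5. The 56% of pairs rests on independent response, with 34% to 68% as the range under the two extremes shown. The effect on the trial's comparisons cannot be sized because the number of repeats is unknown; it is probably small. The reason to act is that the loss cannot be undone and is cheap to prevent.

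**What to change.** Move the check to the second consent, where the address is already collected, before the branch page:

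- Standardise the address, hash it one way with a single secret study-wide salt, and compare it with the hashes of addresses already enrolled.
- Do not re-randomise a match.
- State in advance that the first randomisation counts.
- Keep the hash, not the address, until cleaning ends.
- Report the number of entries blocked.

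The address-deletion rules can then stay as they are.

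At minimum, have the web development manager flag duplicate study numbers before any address is deleted, including the rolling deletions for non-responders, and say so in both privacy sections. This finds repeats but does not prevent the second randomisation.

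The cost is a small programming change and revised privacy wording for the two IRBs. Repeats under different addresses remain undetected, as Quality Assurance already admits.

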## Intervention Participant Exclusion Criteria

• Women and transgender persons

**Exclusion of Women and Transgender Persons**

The purpose of our online intervention is to reduce sexual risk and drug and alcohol use among MSM; therefore, women are excluded from the intervention. Women and male-to-female transgender respondents will automatically be skipped to the last section of the baseline survey on general health. Female-to-male transgender respondents will be able to complete the baseline survey but will not be eligible for the intervention study. No transgender participants will be eligible to participate in the trial since this study is specifically for biologically male participants.

**Exclusion of Children**

This intervention involves men age 18 and over. The NIH definition of children is anyone under the age of 21.47 However, the Public Health Solutions IRB does not permit recruitment of participants under age 18 in online surveys. Additionally, children (those under the age of 18) are excluded from participation because they are likely to be at different cognitive and developmental stages than young adults. Thus, an intervention for minors would necessitate a different intervention approach tailored for their developmental age. Finally, the gay websites we will partner with have a policy against registering anyone under age 18.

If an individual under the age of 18 attempts to participate in the baseline and enters his true age in the assessment, he will automatically and immediately be skipped to the referral page at the end of the survey, which will provide links to HIV testing, drug and alcohol treatment, mental health hotlines, and information about abstinence, mutual monogamy, and consistent condom use.

**Estimated Number of Participants**

The following estimates are based on our previous research (Appendix A). We expect that 10,522 individuals will consent to participate in the baseline behavioral assessment. Eighty percent of these individuals (8,418/10,522) will likely respond to all of the items that assess eligibility for participation in the larger intervention study. Forty-nine percent of these individuals (4,125/8,418) will likely meet the criteria for intervention inclusion, and 73% (3,000) will likely consent to participate in the intervention evaluation study.

**Sampling, Sample Size, and Statistical Power**

The three primary outcomes in this study are increased HIV testing, HIV disclosure, and condom use. Using historical data from the pilot intervention (see Appendix A), we observed that HIV testing increased from 20% to 42% in HIV-negative men between baseline and 3-month follow-up. Based upon these values using a 2-group design (control vs. intervention), with a 5% significance level and 80% power, 77 participants would be required in each study condition for a total sample size of 154. In the current study, which has a 5 branch design, we anticipate that by enrolling 3,000 men and retaining 70% (N=2,111), we will have sufficient power to detect meaningful differences in behavior among the study branches.

Although we will be comparing within and across all study branches, we expect the greatest differences to be found between control branch 1 and branch 5 (both videos) for the primary outcomes. The Bonferroni correction will be used to protect the overall Type I error rate with multiple comparisons. In these comparisons, the nominal significance level will be set to alpha = 0.05 for two-sided tests (divided by the number of pairwise comparisons for individual tests). Using Chi-square tests to detect behavioral changes between the binomial primary outcomes, we obtain the following powers to detect a difference between two study branches for various true proportions and sample sizes (α=0.05; 10 pairwise comparisons).

| **Power Calculations for Meaningful Differences**  **between Study Branches** | | | | | |
| --- | --- | --- | --- | --- | --- |
| **Behavior Change Outcomes†** | | **Sample Size per Branch* and Associated Power** | | | |
| Branch A | Branch B | N = 300 | N = 400 | N = 500 | N = 600 |
| 0.10 | 0.15 | 0.142 | 0.221 | 0.308 | 0.396 |
| 0.10 | 0.20 | 0.709 | 0.865 | 0.944 | 0.979 |
| 0.10 | 0.25 | 0.978 | 0.997 | >.999 | >.999 |
| 0.15 | 0.20 | 0.097 | 0.150 | 0.210 | 0.275 |
| 0.15 | 0.25 | 0.569 | 0.747 | 0.863 | 0.931 |
| 0.15 | 0.30 | 0.939 | 0.988 | 0.998 | >.999 |
| 0.20 | 0.30 | 0.476 | 0.652 | 0.784 | 0.874 |
| 0.20 | 0.35 | 0.894 | 0.971 | 0.993 | 0.999 |
| 0.20 | 0.40 | 0.994 | >.999 | >.999 | >.999 |
| 0.30 | 0.40 | 0.375 | 0.536 | 0.673 | 0.780 |
| 0.30 | 0.45 | 0.821 | 0.936 | 0.980 | 0.994 |
| 0.30 | 0.50 | 0.984 | 0.998 | >.999 | >.999 |
| 0.40 | 0.50 | 0.336 | 0.488 | 0.623 | 0.733 |

†Behavior change outcomes refer to the primary outcomes of interest: HIV disclosure, testing, and condom use.

*We anticipate enrolling 600 per branch; however, attrition may yield smaller sample sizes.

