Participants who drop out of the baseline survey, do not answer questions that assess eligibility, or who drop out before randomization will be considered non-responders. Men who are found ineligible for the intervention component of the study will be shown a script such as “Thank you for your time. We appreciate your input in this study. Here are some links to helpful websites about staying healthy.” Participants will then be shown the survey exit page (example in Appendix G), which will provide links to HIV testing, drug and alcohol treatment, mental health hotlines, and information about abstinence, mutual monogamy, and consistent condom use (ABC). For those who are eligible, the second consent form (Appendix C-2) will be presented immediately after the baseline.

All participants will be scheduled for an online follow-up survey 60 days post-intervention, at which time they will receive an email with a hyperlink to the follow-up. A study reminder (Appendix C) will precede the 60-day follow-up survey (Appendix E) and will contain similar information to the second consent. After reading the reminder, participants will choose whether they would like to continue to the survey or not. Regarding intention to treat (ITT), once participants consent and are randomized, they will be kept in their original assignment group and be sent a link to the 60-day follow-up survey even if they do not participate in the intervention activity (i.e., watch video(s) or view standard prevention web page) or answer the post-intervention questions.

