***Title: Is HIV Still a Big Deal?***

***Baseline***

[name], PI

Between October 11 and 22, 2005 we conducted our first national online behavioral intervention on Manhunt.net (funding from the van Ameringen Foundation, The New York Community Trust, and The Shelley and Donald Rubin Foundation). **The Morning After** was designed to promote critical thinking about HIV disclosure, risky sexual behaviors and the complex beliefs and attitudes underlying these behaviors. Approximately 13,500 men clicked on the online banner ad, and out of those, 3,139 consented to participate in the intervention; 2,777 completed the baseline behavioral risk survey (pre-test); 1601/2777 watched the video about a sexual encounter between an HIV-positive and HIV-negative male; 1510/1601 completed the questions about HIV testing and disclosure after the video (post-test); and 1087/1510 consented to give us their email address for a follow-up behavioral risk survey in 3 months. Online, 1,002 men completed the baseline behavioral survey, watched the video, completed the post-video survey and provided valid email addresses for 3 month follow-up. The median age of men consenting to participate was 38.

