***Follow-up*: Validation of the Online Video as an Intervention**

Of the 1,002 men who completed the survey and provided emails, 3 months later, 908 emails were still working. Emails linking to the follow-up survey were sent 1/17, 1/23 and 2/1/06 to 908/1,002. No incentives were provided. Preliminary analysis compared disclosure of HIV status to sexual partners and HIV testing, before and in the 3 months after watching the video, by McNemar and Pearson Chi-square tests. Three months after watching the video, 496 of 908 men (55%) with working emails completed the follow-up survey. Men completing follow-up and those who did not were similar by race/ethnicity (14% Hispanic, 72% white, 6% black, 2% Asian, 6% mixed/other), age (mean 38) and prevalence of unprotected anal intercourse with a new/casual partner (36%), but were significantly more likely to have a college degree (55% vs. 47%, p=.01). Statistically significant behavior changes were found. Men were 3 times more likely to ask their partner’s HIV status (OR=3.0, p<.001) and two times more likely to disclose their own(OR=2.2, p<.001) at follow-up compared to baseline. The 318 HIV-negative men participating in the evaluation were also three times more likely to report HIV testing during follow-up (42%) than in the 3 months before baseline (20%) (OR=2.8, p<.001). These findings strongly suggest that online interventions designed to engage critical thinking are an efficient and effective way to influence behavior change in large numbers of at-risk MSM.

We examined the prevalence and stability of drug and alcohol use between baseline and follow-up. At baseline, 7% reported methamphetamine use in their last sexual encounter. At follow-up, 5% reported methamphetamine in their last encounter. Out of the methamphetamine users at baseline, 39% followed up and were significantly LESS likely than non-users to follow-up (OR 0.6, p<.05). Contrary to methamphetamine use, other drug use (i.e., poppers, marijuana, MDMA, GHB, cocaine) as well as alcohol use, reported between baseline and follow-up remained stable. Specifically, there were no significant differences in the proportions of men reporting drug or alcohol use at baseline compared to follow-up. Drug use at baseline and follow-up was 24% and 32%; alcohol use was 27% at both baseline and follow-up.

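### The 77-per-condition figure for HIV testing treats an uncontrolled 3-month pilot change as a between-branch difference, and the power table's N for HIV testing ignores serostatus

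*Protocol*

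**What the plan says.** Sampling, Sample Size, and Statistical Power starts from the pilot: "we observed that HIV testing increased from 20% to 42% in HIV-negative men between baseline and 3-month follow-up". It puts these rates into a two-group, control-versus-intervention calculation and concludes that "with a 5% significance level and 80% power, 77 participants would be required in each study condition for a total sample size of 154". The next sentence says that 3,000 enrolled and 2,111 retained men will give sufficient power across five branches. A power table follows, for 300 to 600 men per branch, at a two-sided 0.05 divided by 10 pairwise comparisons. Its footnotes say that "Behavior change outcomes refer to the primary outcomes of interest: HIV disclosure, testing, and condom use", and that 600 per branch may fall because of attrition. No other reduction is mentioned.

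Other sections bear on these inputs:
- Appendix A describes the pilot as one group compared before and 3 months after the video. Everyone followed up had watched it. Of the 496 men who completed follow-up, 318 were HIV-negative and taking part in the evaluation.
- The inclusion and exclusion criteria do not exclude HIV-positive men.
- Additional Measurements restricts the HIV testing intention item to HIV-negative men, and Appendix F restricts it to negative or untested men.
- Data Handling and Analysis names the outcome as HIV testing in the 60 days after baseline.
- Participant Recruitment and Enrollment Procedures, under intention to treat, keeps men in their assigned group and sends them the follow-up link "even if they do not participate in the intervention activity".

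**The concern.** There are two separate problems.

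The first is the contrast. A before-after change in one group includes whatever would have happened without the video: background testing, regression to the mean, the effect of being surveyed, and selection of men who return. A randomised comparison removes these. Using the whole change as the expected difference between branches credits all of it to the video. The calculation also uses a 3-month window and alpha 0.05, whereas the branches are compared over 60 days at 0.005.

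The second is the denominator. The rates come from HIV-negative men, but the table's N counts all men. HIV-positive men cannot contribute to a testing outcome, so the usable N for this outcome is smaller than the N for disclosure or condom use.

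HIV testing is one of three named primary outcomes. If its power is overstated, a null result could be read as absence of effect when the comparison was too small to show a moderate one.

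**Working it through.** **Inputs.** Pilot rates 20% and 42%, and alpha 0.05/10 = 0.005 (Sampling, Sample Size, and Statistical Power). Retained men: 600 − 240 = 360 in branches 1 and 2, and 600 − 180 = 420 in branches 3 to 5 (Attrition and Retention Efforts). HIV-negative share in the pilot: 318/496 = 64.1%. Pilot watching share: 1,601/2,777 = 57.7% (Appendix A). The protocol gives no testable share for this trial, so 80% and 90% are my assumptions.

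**Step 1: reproduce the 77.** With d = |p1 − p2| and p̄ the mean rate:
- n = [z(α/2)·√(2p̄(1−p̄)) + z(β)·√(p1(1−p1) + p2(1−p2))]² / d²
- continuity-corrected n = (n/4)·[1 + √(1 + 4/(n·d))]²

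For 20% v 42% at two-sided 0.05 and 80% power, n = (1.960×0.654 + 0.842×0.635)²/0.22² = 68.2. The corrected value is 77.0, which matches.

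**Step 2: reproduce the table.** Power = Φ{[d − ½(1/n1 + 1/n2) − z(α/2)·√(p̄(1−p̄)(1/n1 + 1/n2))] / √(p1(1−p1)/n1 + p2(1−p2)/n2)}, with p̄ weighted by group size. At alpha 0.005 the largest deviation from any numeric cell is 0.013. The arithmetic is sound.

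**Step 3: use the trial's alpha and window.**
- 20% v 42% at 0.005: n = 116.1, corrected to 125.0 per group.
- Constant-rate conversion from 90 to 60 days (assumption): 1 − 0.80^(2/3) = 13.8%, and 1 − 0.58^(2/3) = 30.5%.
- 13.8% v 30.5% at 0.005: n = 164.4, corrected to 176.2 per group.

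**Step 4: correct the denominator.** Branch 1 v branch 5 at 0.005:

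| Testable share | N | 20% v 30% | 13.8% v 30.5% |
|---|---|---|---|
| All men | 360 v 420 | 0.624 | 0.997 |
| 90% | 324 v 378 | 0.557 | 0.993 |
| 80% | 288 v 336 | 0.485 | 0.983 |
| 64% | 231 v 269 | 0.362 | 0.942 |

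The 64% is probably a lower bound. It counts HIV-negative men only, and Appendix A does not give the status of the other 496 − 318 = 178 completers, some of whom may be untested.

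**Step 5: men who do not watch.** Suppose they do not change and stay in the comparison. The video-branch rate is then 13.8% + w×(30.5% − 13.8%), where w is the watching share.
- w = 80% (assumed): 27.1%. Power is 0.77 (64% testable) to 0.93 (90% testable).
- w = 57.7% (pilot share): 23.4%. Power is 0.42 to 0.63, and 80% power needs about 458 per group.

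**Step 6: part of the pilot rise not due to the video.** Halving the 60-day difference gives (30.5% − 13.8%)/2, about 8.3 points; the half is illustrative. Above an unchanged control rate (13.8% v 22.1%), power is 0.30 to 0.47 for 64% to 90% testable. If the other half of the rise also occurs in the control branch (22.1% v 30.5%), it is 0.21 to 0.34.

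**The case against.** The strongest reply is that the 20% and 42% produce only the 77/154. They do not set the 3,000, and the table is a generic grid at 0.005 into which the pilot figures do not enter. The 77 is openly a two-group illustration and was worked out for HIV-negative men, with the Bonferroni correction in the next paragraph. At the full pilot effect, power stays at 0.94 or more even with 64% testable. All of this stands.

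A reader might infer that HIV testing is badly underpowered, with power near 0.42. The documents do not support that as an expectation. The figure needs the pilot's 58% watching share, which Appendix A measures among baseline completers ("1601/2777 watched the video about a sexual encounter between an HIV-positive and HIV-negative male") before emails were requested. Here men are randomised only after a second consent and supplying an email, and the calculation concerns those who also complete follow-up. Applying 58% to them is a pessimistic case. The intention-to-treat text also covers only assignment and follow-up; it does not define an analysis set.

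A reader might also set the table's 0.652 (20% v 30%, N = 400) against 0.36. That mixes attrition with eligibility and takes the lowest share. Like for like, 0.62 falls to 0.56 at 90% testable. HIV prevalence in the sponsor's earlier online samples (8% overall in one, 3% to 16% and 4% to 22% by age group in the others) points to a share nearer 80% to 90% than 64%. The table's N = 300 column already shows 0.476 for this row, although the footnote links smaller N only to attrition.

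The reply does not remove two facts: the pilot rates are not a control-versus-intervention contrast, and the footnote's N for HIV testing is not reduced for serostatus.

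**Conclusion.** The concern holds in this limited form, at minor to moderate severity. The 77 per condition does not justify a between-branch comparison in this trial. About 125 per group are needed for the same rates at 0.005, and about 176 on the 60-day scale under a constant rate. Both numbers are below the planned testable completers, so if the whole pilot effect were causal and everyone watched, the trial would still be adequately powered.

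The footnote overstates the N for HIV testing. The cost for 20% v 30% is a fall from 0.62 to between 0.36 and 0.56, depending on a testable share of 64% to 90% that the protocol does not give.

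The larger uncertainty is how much of the pilot rise would appear between branches. The protocol gives neither a control rate nor an expected watching share after the second consent, so the results in steps 5 and 6 show sensitivity and are not forecasts. The fault is in the inputs, not the arithmetic.

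**What to change.** 1. Stop using 77/154 as justification for a between-branch comparison. If the pilot result is kept as background, describe it as an uncontrolled before-after change over 3 months in men who had watched the video.
2. Give HIV testing its own power line: negative or untested completers per branch, 60-day rates, alpha 0.005, and stated ranges for the testable share, the watching share and the part of the pilot rise credited to the video.
3. Amend the table footnote to say that N for HIV testing is reduced by serostatus as well as by attrition.

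The cost is some wording and one recomputed line. Enrolment does not change. The only downside is a less favourable stated power for this outcome.
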